#### Demographic Information Analysis

For both patients with PD and healthy participants, continuous data will be presented as mean (SD) or as median, minimum, maximum, and 95% CIs, whereas categorical data will be shown as frequencies and percentages.

#### Analysis for Changes in Clinical Outcomes

For the following clinical outcomes with continuous variables, the mean (SD), median, minimum, maximum, and maximum of each outcome will be presented for change in score from day 0 to 6 weeks, 12 weeks, and 20 weeks, and a 1-way repeated measures ANOVA will be performed to test for statistically significant changes in any of the following factors: total MDS-UPDRS score, total MDS-UPDRS score part I score, total MDS-UPDRS part II score, total MDS-UPDRS part III score, total MDS-UPDRS part IV score, BBS, TUG, S&E, PDQ-39, levodopa dosage investigation, abdominal examination, GSRS, TDS, BSS, and MYMOP.

#### Changes in Gut Microbiome–Related Metabolites and Gut Microbiome

Differences in microbiome at each time point will be measured using weighted-unweighted UniFrac distance metrics and subsequently tested using analysis of similarity (ANOSIM). Correlations of clinical outcomes and treatment effects with key microbiomes will be analyzed using Spearman rank correlation analysis, with *P*<.05 considered significant. Principal component analysis will be applied to analyze metabolite distribution in the sample. Partial least squares-discriminant analysis will be applied to identify differences between patients with PD and healthy participants when analyzing metabolite distributions. Selected gut microbiome and metabolite changes will be analyzed by 1-way repeated measures ANOVA, with significant differences between time points determined at *P*<.05. The pathway analysis or enrichment analysis will be performed to analyze the metabolic pathways of the selected metabolites. The Kyoto Encyclopedia of Genes and Genomes database [39] will be used to identify interactions between metabolites. Receiver operating characteristic analysis will be conducted to confirm whether the selected metabolites reflect the representativeness of the disease or treatment.

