#### Evaluation of Gut Microbiome–Related Metabolites and Gut Microbiome Change

Blood samples will be used to assess changes in gut microbiome–related metabolites. Blood will be collected from participants after an 8-hour fast before blood collection, and changes in metabolites will be determined using liquid chromatography-mass spectrometry and gas chromatography-mass spectrometry analyses. Western blotting will be applied to confirm changes in strain-derived factors in the blood of patients with PD. Participants’ fecal samples will be used to analyze the composition of the gut microbiome using 16S rRNA sequencing and fecal microbiome transplantation to assess the correlation between gut microbiome and response to acupuncture treatment. A small amount of feces will be collected using 4N6 FLOQSwabs (Copan Diagnostics Inc). For participants with PD, 2-3 g of feces will be collected using a Stool Collection Tubes With DNA Stabilizer (Invitek Diagnostics) for fecal microbiome transplantation. A FastDNA SPIN Kit for Feces (MP Biomedicals) will be used to isolate DNA from feces for DNA extraction and sequencing. DNA will be subjected to polymerase chain reaction targeting the V3-V4 variable region of bacterial 16S rRNA as a template, followed by sequencing library construction and sequencing reactions on the MiSeq Platform (Illumina, Inc). Sampling will be conducted at day 0, 6 weeks, 12 weeks, and 20 weeks in participants with PD and after screening in healthy participants.

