### Sample Size

This study is not intended to statistically validate the intervention effect of acupuncture and moxibustion on PD but was rather conducted as an exploratory study comparing gut microbiome markers in patients with PD and healthy participants and the effects of acupuncture and moxibustion on the gut microbiome in patients with PD. Therefore, the sample size required for the study will be 60 patients with PD and 20 healthy individuals, depending on the financial resources and study environment, and in consultation with experts in gut microbiology.

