This protocol has limitations. First, as this study was designed as a single-group, prospective observational study with a primary focus on analyzing pre-post changes of patients with PD, a control group of healthy participants was included for baseline comparison rather than incorporating a control group within the PD cohort. This limits the internal validity of the intervention findings, as changes may be influenced by natural disease progression or placebo effects rather than the treatment itself. Second, although the sample size was determined based on feasibility rather than statistical power calculations, 60 patients with PD and 20 healthy participants may limit the reliability and generalizability of both within-group and between-group comparisons and increase the risk of type II error. Third, as no blinding was applied, the use of subjective, patient- and clinician-reported outcomes such as MDS-UPDRS, PDQ-39, and MYMOP increases the risk of detection and expectation bias, potentially compromising causal inference in this single-arm design. Fourth, adverse events are assessed by the treating Korean medicine doctors without independent adjudication or standardized grading criteria, which may limit the objectivity and consistency of safety reporting in this study. To address these limitations, future studies should adopt an RCT design with an adequately powered sample size, blinding procedures, and standardized outcome and safety assessments to enhance the internal validity, causal inference, and generalizability.

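### The ANOSIM test of microbiome change over time specifies no blocking by patient; in its standard form it is conservative for these repeated samples and can miss a small to moderate shift

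*Protocol article*

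**What the plan says.** Under Changes in Gut Microbiome–Related Metabolites and Gut Microbiome, the community-level analysis is one sentence: "Differences in microbiome at each time point will be measured using weighted-unweighted UniFrac distance metrics and subsequently tested using analysis of similarity (ANOSIM". It gives no stratum, block or permutation scheme.

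The sampling schedule, under Evaluation of Gut Microbiome–Related Metabolites and Gut Microbiome Change, is: "Sampling will be conducted at day 0, 6 weeks, 12 weeks, and 20 weeks in participants with PD and after screening in healthy participants".

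The analysis section that contains the ANOSIM sentence also names a paired method, but for other quantities: "Selected gut microbiome and metabolite changes will be analyzed by 1-way repeated measures ANOVA", "with significant differences between time points determined at *P*<.05". The clinical outcomes are given repeated measures ANOVA as well.

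On size and purpose, the Sample Size section says "This study is not intended to statistically validate the intervention effect of acupuncture and moxibustion on PD" and sets no effect size or power target. The Discussion accepts a risk of type II error and ties it to the number of participants: "although the sample size was determined based on feasibility rather than statistical power calculations".

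**The concern.** The ANOSIM sentence can only concern the comparison over time. Healthy participants are sampled once, and PD versus healthy has its own section with a t test or Mann-Whitney test. The four groups are therefore the same people at four visits.

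Standard ANOSIM is a one-way test. It asks whether samples from different visits are less alike than samples from the same visit, and it builds its reference distribution by exchanging visit labels across all samples. With repeated samples this goes wrong in two ways. Every pair of samples from one patient falls in the between-visit set, and such pairs are alike, which pulls the statistic down. Free relabelling also breaks the pairing, so stable differences between patients become noise in the reference distribution.

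At stake is the stated objective of describing how the gut microbiome changes with treatment. A real change could be returned as null, and the Discussion would lead a reader to blame the sample size when the cause is the test.

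**Working it through.** **Inputs.** From the protocol article: 60 patients with PD; four samples each (day 0 and weeks 6, 12 and 20); ANOSIM on UniFrac distances. The 0.05 level is stated for the repeated measures ANOVA and assumed here for ANOSIM. The article gives neither the within-patient correlation nor an expected shift, so both are assumptions: ICC 0 to 0.9, shift 0 to 0.7 SD. It states no power figure, so there is none to reproduce.

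**Step 1: why the statistic is pulled down.** ANOSIM uses R = (mean rank of between-visit distances − mean rank of within-visit distances) / (M/2), where M is the number of pairs.

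- Samples: 60 × 4 = 240. Pairs: M = 240 × 239 / 2 = 28,680.
- Within-visit pairs: 4 × 60 × 59 / 2 = 7,080. All join different patients.
- Between-visit pairs: 28,680 − 7,080 = 21,600, of which 60 × 6 = 360 join two samples of one patient.

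Suppose nothing changes over time and patients are so distinct that these 360 pairs hold the lowest ranks. Their mean rank is (1 + 360)/2 = 180.5, and that of all other pairs is (361 + 28,680)/2 = 14,520.5. Then R = (360/21,600) × (180.5 − 14,520.5) / 14,340 = −1/60 = −0.0167. Free permutation expects R near 0, so the observed value starts below its own null. The simulated mean R under no change is 0.0004, −0.0097, −0.0146, −0.0166 and −0.0167 at ICC 0, 0.3, 0.5, 0.7 and 0.9, approaching this limit.

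**Step 2: rejection rates.** The simulation had 60 patients × 4 visits and 20 Gaussian features with total SD 1. The shift was in 5 features (half at week 6, full at weeks 12 and 20). Distances were Euclidean, with 199 permutations, alpha 0.05 and 150 runs per cell. Entries are % rejected: unrestricted / within patient, using the same ANOSIM statistic.

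| ICC | no change | 0.2 SD | 0.3 SD | 0.4 SD | 0.5 SD | 0.6 SD |
|---|---|---|---|---|---|---|
| 0 | 4.7 / 4.0 | 19 / 17 | 39 / 39 | not run | 97 / 99 | not run |
| 0.3 | 0.7 / 4.7 | 0.7 / 22 | 3 / 61 | 34 / 93 | 78 / 100 | 98 / 100 |
| 0.5 | 0 / 6.7 | 0 / 33 | 0 / 78 | 7 / 100 | 51 / 100 | 93 / 100 |
| 0.7 | 0 / 2.0 | 0 / 55 | 0 / 97 | 0.7 / 100 | 37 / 100 | 95 / 100 |
| 0.9 | 0 / 4.0 | 0 / 100 | 0 / 100 | 0 / 100 | 25 / 100 | 99 / 100 |

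At 0.7 SD the unrestricted test reaches 100% at every ICC run (0.3 to 0.9). The simulation standard error at 5% is √(0.05 × 0.95 / 150) = 1.8 points, so the 2.0% to 6.7% under within-patient permutation agrees with the nominal level.

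**Step 3: one-variable cross-check.** Compare two visits, n = 60, ICC 0.5, shift 0.3 SD. An unpaired test assumes a standard error of √(2/60) = 0.183, while the true one is √(2 × 0.5/60) = 0.129.

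- Unpaired size: 2 × [1 − Φ(1.96 × 0.183/0.129)] = 0.6%.
- Unpaired power: Φ((0.3 − 1.96 × 0.183)/0.129) = 33%.
- Paired power: Φ(0.3/0.129 − 1.96) = 64%.

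At ICC 0.7 the size is 0.03% and the powers are 28% and 85%. The direction is the same.

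**Step 4: does the statistic matter?** A further simulation (4 of 20 features shifted by 0.3 SD, ICC 0.5 to 0.7, 99 permutations, 200 runs for two visits and 100 for four) compared two tests, both permuted within patient. Two visits: ANOSIM 75–96%, PERMANOVA 79–98%. Four visits: 80–95% and 83–95%. Unrestricted ANOSIM gave 2–4% and 0%. Nearly all the gain comes from the permutation scheme.

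**The case against.** The strongest reply is that the defect is inferred from silence. The article does not say that permutations are unrestricted, ANOSIM can be run within patient, and a condensed article may leave the permutation stratum to an analysis plan that is not shown. This stands to the extent that nobody can say the wrong analysis has been chosen. It does not remove the point. The article names the test, names a repeated measures method elsewhere in the same section, and leaves the community-level test over time as the one without it. An analyst following the text would run the standard form.

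A reader might go further and infer that the trial has almost no power for its main question. The documents do not support that, for three reasons.

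- The loss depends on an ICC and a shift that the article does not give. Power is very low up to about 0.3 SD at ICC 0.3 and about 0.4 SD at ICC 0.5 or more, but at least 93% at 0.6 SD. At ICC 0 nothing is lost.
- The named primary outcome is MDS-UPDRS, and the study is described as exploratory.
- Selected taxa and metabolites still receive a paired analysis, so ANOSIM is not the only test of microbiome change.

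It is also fair that the error is conservative and creates no false claim of change. But an exploratory study has reason to avoid discarding real signals, and an analysis of selected taxa does not replace a whole-community test. Finally, the results do not show that ANOSIM must give way to PERMANOVA.

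**Conclusion.** The concern holds in a limited form. As written, the community-level test over time does not account for four samples per patient. If run in its standard form, its type I error falls from about 5% at ICC 0 to under 1% at ICC 0.3 and to 0 of 150 runs at ICC 0.5 or more. At ICC 0.5 it detects 0%, 7% and 51% of shifts of 0.3, 0.4 and 0.5 SD, where the same statistic permuted within patient detects 78%, 100% and 100%. By 0.6 SD the unrestricted test recovers to 93%.

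The step 1 arithmetic gives the direction of the bias whenever samples from one patient resemble each other. The percentages rest on assumed ICCs and shifts, Gaussian features and Euclidean distances in place of UniFrac, and complete sampling of 60 patients, so they are illustrative. The consequence is a possible false null on a stated objective, not on the primary outcome.

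**What to change.** State that for the comparison across day 0 and weeks 6, 12 and 20, permutations are restricted to within patient (patient as block). Either ANOSIM or PERMANOVA on the same weighted and unweighted UniFrac matrices will do. Apply the same restriction to any contrast of a later visit with day 0. Three such contrasts on two matrices make 3 × 2 = 6 tests, so either treat them as secondary to the overall test or adjust them for multiplicity.

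The cost is one or two sentences in the analysis text and one setting in the permutation call, with no new data. The Results section says that observation has ended and analysis is under way, so the choice should be recorded and dated before the community-level result is relied on. If within-patient permutation was always intended, saying so closes the point.

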## Methods

### Study Design

This protocol describes a single-group, prospective, observational study aiming to analyze differences in gut microbiome between patients with idiopathic PD and healthy participants, to observe changes in gut microbiome after 12 weeks of acupuncture and moxibustion in patients with PD, and to correlate these changes with changes in motor and nonmotor symptoms of PD that were altered by acupuncture and moxibustion treatment. The gut microbiome patterns at baseline in healthy participants and screened patients with PD will be analyzed to determine whether the gut microbiome of patients with PD is different from that of healthy participants. Patients with PD will be treated with acupuncture, moxibustion, and intradermal acupuncture twice a week for 12 weeks, yielding a total of 24 sessions. The motor and nonmotor symptoms of PD and gut microbiome changes in response to acupuncture and moxibustion will be compared before starting treatment (day 0), during treatment (6 weeks), at the end of treatment (12 weeks), and 2 months after the end of treatment (20 weeks). The correlation between motor and nonmotor symptoms of PD changed by acupuncture and moxibustion treatment and changes in gut microbiome will be analyzed. The enrollment, interventions, and assessments of patients with PD are summarized in Table S1 in Multimedia Appendix 1. A schematic of the study process is shown in Figure 1. Healthy participants will be assessed for motor and nonmotor symptoms of PD and gut microbiome after screening. The enrollment and assessment of healthy participants are summarized in Table 1. Kyung Hee University Korean Medicine Hospital, Seoul, Republic of Korea, will serve as the study site. The study protocol was registered with the Clinical Research Information Service (KCT0006669) on October 15, 2021. This protocol was reported in accordance with the SPIRIT (Standard Protocol Items: Recommendations for Interventional Trials) guidelines (Multimedia Appendix 2).

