#### Evaluation of Motor and Nonmotor Symptoms of PD

The MDS-UPDRS, the primary outcome of this study, was developed to complement the UPDRS as a tool to assess motor and nonmotor symptoms in patients with PD [22], and the Korean version has been validated [23]. The MDS-UPDRS comprises the following four parts with a total of 65 items: (1) nonmotor experiences of daily living, (2) motor experiences of daily living, (3) motor examination, and (4) motor complications. Of these, 48 items are scored from 0 to 4, with 0 (robust), 1 (slight), 2 (mild), 3 (moderate), and 4 (severe), and the 17 remaining items are scored as yes or no. Scores are calculated by summing the scores for each item, with higher scores indicating more severe symptoms of PD. The BBS is used to assess balance [24] and is also useful in evaluating equilibrium in patients with PD [25], and the Korean version of this tool has been validated [26]. This tool comprises 14 items that are scored from 0 (worst) to 4 (best), and the total score is evaluated. The TUG is used for assessing gait in older adults [27] and is used to evaluate walking ability in patients with PD [28]. This test measures the time taken to get up from a chair, walk around a 3-meter return point, and return to the chair in the initial position. The S&E is a component of the UPDRS that evaluates functional independence and is widely used as a standard Parkinson assessment tool [29]. The patient’s function is evaluated using an 11-point scale with 10% increments, from 100% (completely independent) to 0% (vegetative functions are not functioning or bedridden). The PDQ-39 is used for assessing health-related quality of life (HrQoL) in patients with PD [30], and the Korean version has been validated [31]. The PDQ-39 comprises 8 dimensions with 39 items. Each item is scored from 0 (never) to 4 (always), with a higher total score indicating poorer HrQoL due to PD. Levodopa dosage investigation includes assessment of the daily dose and number of levodopa doses administered to patients with PD. Changes in type and dose of levodopa from pretreatment will be investigated first as “yes or no” and then dichotomized into “decrease or increase” for participants with no change for comparison between groups. Evaluation will be conducted at day 0, 6 weeks, 12 weeks, and 20 weeks in participants with PD and after screening in healthy participants.

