### Statistical Analysis

#### Overview of Statistical Analysis

SPSS (ver 21.0, IBM SPSS Statistics for Windows) will be used for analysis. All measures will be presented as mean (SD) for continuous variables and as n (%) for dichotomous variables. For efficacy endpoints, the amount of change or rate of change from baseline to end of treatment and follow-up will be calculated.

All data obtained from participants will be analyzed in 2 forms: intention-to-treat (ITT) analysis and per-protocol (PP) analysis. The ITT analysis will be performed on all participants who undergo acupuncture and moxibustion at least once. For missing data on the evaluation variables, the last observation carried forward (LOCF) method will be applied. PP analysis will further be performed on participants who completed the entire study. The evaluation will be based on the results of the ITT analysis and is presented with reference to the PP analysis.

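### The symptom–microbiome correlation ignores the day-0 values already collected, so a significant result may only reflect linked starting levels; an adjusted correlation should be reported beside it

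*Protocol article*

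**What the plan says.** Study Design in the protocol article sets the aim "to correlate these changes with changes in motor and nonmotor symptoms of PD that were altered by acupuncture and moxibustion treatment" and repeats it: "The correlation between motor and nonmotor symptoms of PD changed by acupuncture and moxibustion treatment and changes in gut microbiome will be analyzed". The abstract and the Evaluation Overview describe the same association.

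The method is in the section on changes in gut microbiome–related metabolites and gut microbiome: "Correlations of clinical outcomes and treatment effects with key microbiomes will be analyzed using Spearman rank correlation analysis", "with *P*<.05 considered significant". It names no covariate and no partial correlation.

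The Overview of Statistical Analysis says that, for efficacy endpoints, "the amount of change or rate of change from baseline to end of treatment and follow-up will be calculated". The choice between amount and rate is not made, and the form of change for taxa and metabolites is not stated.

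The starting values exist for both sides. For symptoms: "Evaluation will be conducted at day 0, 6 weeks, 12 weeks, and 20 weeks in participants with PD". For stool and blood: "Sampling will be conducted at day 0, 6 weeks, 12 weeks, and 20 weeks in participants with PD".

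**The concern.** A change score usually depends on the value it starts from. If patients who start worse on symptoms also start further out on a taxon, and both measures move more when they start further out, the two changes will be correlated through baseline alone. An unadjusted Spearman test cannot tell that situation apart from one in which patients whose microbiome shifted more also improved more for the same starting point.

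The distinction matters because there is no PD control group and the Discussion looks to the study for evidence of a gut–brain mechanism. The limitations paragraphs discuss the missing control group, lack of blinding, diet and levodopa dose. They do not mention dependence on starting level.

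The rate-of-change option adds a smaller problem. It divides by the day-0 value and is undefined when that value is zero. Zero is possible on the TDS (items from 0), the MYMOP (0 to 6) and MDS-UPDRS part scores (items from 0), and it would be possible for absent taxa if the rate were also used for them.

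**Working it through.** **Inputs from the protocol.** There are 60 patients with PD (Sample Size); healthy participants have one assessment and contribute no change. Significance is P<.05, taken here as two-sided. The protocol gives no power or error figure for this correlation that could be reproduced.

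**Assumed inputs.** None of these is in the protocol. ρ is the day-0 correlation between symptom and taxon. k is the correlation of baseline with follow-up. b is the share of the starting deviation that is lost. σ is the SD of independent change. R is the day-0 reliability. True baseline SD is 1. In every model the two changes are unrelated given baseline.

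**Critical value.** At n=60, |r| must exceed t/√(58+t²) = 0.254.

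**Model A, regression to the mean with equal SDs.** The induced correlation of changes is ρ(1−k)²/[2(1−k)] = ρ(1−k)/2.

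| ρ | k | Induced r | Raw test rejects |
|---|---|---|---|
| 0 | 0.3–0.9 | 0 | 4.8%–5.0% |
| 0.3 | 0.7 | 0.045 | 6.2% |
| 0.3 | 0.5 | 0.075 | 8.7% |
| 0.5 | 0.5 | 0.125 | 14.4% |
| 0.5 | 0.3 | 0.175 | 24.6% |

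**Model B, room to improve, no measurement error.** The induced correlation is ρb²/(b²+σ²). With b=0.5 and σ=0.5, ρ=0.3 gives 0.3×0.25/0.50 = 0.15 (19.5% rejected) and ρ=0.5 gives 0.25 (45.2%). With b=0.5 and σ=0.3, ρ=0.5 gives 0.5×0.25/0.34 = 0.368 (79.4%). With ρ=0 rejection stays at 4.8%–5.2%, however strongly each change depends on its own baseline.

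In Models A and B, the partial Spearman given both day-0 ranks rejects in 4.5%–5.5% of runs.

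**Model C, room to improve with measurement error.** Each observed change also carries two errors of variance (1−R)/R, so the induced correlation is ρb²/[b²+σ²+2(1−R)/R]. With ρ=0.5, b=0.5, σ=0.3:

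- R=0.9: 0.5×0.25/(0.25+0.09+0.222) = 0.222, just under the critical value. Simulation rejects in about 37%.
- R=0.5: 0.5×0.25/(0.25+0.09+2) = 0.053. Simulation rejects in about 7%.

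Over ρ 0.2–0.5, b 0–0.5 and R 0.5–0.9, raw rejection runs from about 4% to 37%. Adjusted rejection was 4%–7.5%. A repeat run for this write-up gave 4.5%–8.3%, the maximum being at R=0.5, ρ=0.5, b=0.

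**Model D, where adjustment harms.** True levels are stable and correlated, and observed change is only independent measurement error.

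| R | True ρ | Raw | Adjusted |
|---|---|---|---|
| 0.7 | 0.5 | 5.1% | 7.3% |
| 0.5 | 0.5 | 5.3% | 8.8% |
| 0.7 | 0.8 | 4.9% | 15.7% |
| 0.5 | 0.8 | 5.3% | 17.8% |

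Conditioning on a noisy baseline removes only part of the true level, and the remainder is correlated between the two measures. A separate simulation put the upper end at 19%.

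**The case against.** The strongest reply is that the artefact needs a day-0 correlation between severity and taxon level among patients, and the protocol states none. Its planned baseline contrast is PD against healthy participants, and entry is limited to Hoehn and Yahr stage 2–3, which narrows the severity range. This stands: the size is unknown and may be nil.

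A reader might infer proportional change from the Discussion's account of acupuncture restoring the microbiome. That account is a group-level result in an experimental PD model and says nothing about individual patients here. A reader might also infer that room to improve on both sides is enough. Model A at ρ=0 shows that it is not. Nor are the changes simply unrelated when the artefact occurs: they are associated marginally and unrelated only given baseline.

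A third tempting reading is that the adjusted test should replace the planned one. Model D rules that out as a general rule.

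The correlation should not be described as the only planned link between microbiome and response. The protocol also plans fecal microbiome transplantation for that purpose. The Spearman correlation is the only statistical test named for it.

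Finally, the study is described as exploratory, and covariates may be set in an analysis plan not shown. That lowers the weight of the point. It does not remove it, because the article names a specific unadjusted method and a significance threshold for a change-against-change question.

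**Conclusion.** The point holds as a moderate one about interpretation. The planned test is not invalid. It holds about 5% if the baselines are uncorrelated or if change does not depend on starting level. If both conditions are present, raw rejection reaches about 37% over the assumed range with measurement error, and higher in the error-free room-to-improve settings. Adjustment for both day-0 values brings it to about 4%–8% over the range with measurement error. All of these figures rest on assumed correlations, slopes and reliabilities.

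A reader might expect adjustment to raise power as well. No material gain should be claimed: with independent day-0 errors the simulated gain was 0 to 6 percentage points.

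Leaving amount or rate of change open is a genuine but small defect for these correlations.

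**What to change.** In the section on changes in metabolites and gut microbiome, keep the planned Spearman correlation. Beside it, add a partial Spearman correlation of symptom change with taxon or metabolite change, adjusted for the day-0 symptom score and the day-0 taxon or metabolite level. State that a symptom–microbiome link will be called independent of starting level only if both analyses support it, and that disagreement will be reported as such. For these correlations, fix absolute change from day 0 and drop the rate of change.

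The cost is a few lines of text and code and two degrees of freedom (60−2=58 becomes 60−4=56). No new data are needed. The adjusted test can exceed 5% when day-0 measures are noisy and strongly correlated, so the pair must be read together. The article reports that data analysis is under way. If the correlations have already been seen, the adjusted version should be labelled as added afterwards.

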#### Comparative Analysis of the Gut Microbiome Between Healthy Participants and Patients With PD

Differences in gut microbiome between healthy participants and patients with PD will be determined by testing the acquired data for normality and performing a parametric test with an independent *t* test if the population is normal or a nonparametric test with the Mann-Whitney *U* test if the population is not normal.

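### An unadjusted P<.05 is fixed for correlating an uncounted set of key taxa with up to 15 clinical outcomes, so about 0.75 chance links are expected per taxon per change time

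*Protocol article*

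**What the plan says.** The rule is in the Statistical Analysis section, under *Changes in Gut Microbiome–Related Metabolites and Gut Microbiome*: "Correlations of clinical outcomes and treatment effects with key microbiomes will be analyzed using Spearman rank correlation analysis, with *P*<.05 considered significant". The same subsection applies the threshold again: "Selected gut microbiome and metabolite changes will be analyzed by 1-way repeated measures ANOVA, with significant differences between time points determined at *P*<.05". Neither sentence mentions adjustment, and no false discovery rate, Bonferroni or similar method appears elsewhere in the article.

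The clinical outcomes are listed under *Analysis for Changes in Clinical Outcomes*. They are the MDS-UPDRS total and its four parts, followed by "BBS, TUG, S&E, PDQ-39, levodopa dosage investigation, abdominal examination, GSRS, TDS, BSS, and MYMOP". That is 5 + 10 = 15. That subsection describes each as a "change in score from day 0 to 6 weeks, 12 weeks, and 20 weeks", so three change scores exist per outcome.

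The taxa enter only as "Correlations of clinical outcomes and treatment effects with key microbiomes". No count, taxonomic level or selection rule is given, and the sentence does not say which of the three change scores are correlated.

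**The concern.** According to *Study Design*, relating microbiome change to symptom change is one of the study's aims, and it is the analysis that ties the gut findings to the symptoms. A rule that accepts each correlation at P<.05 will return a list of significant gut-symptom links even when no taxon is related to any symptom. The reader of the results could not tell that list from a real one, since neither the size of the search nor the selection of the taxa is fixed. There is no untreated PD group whose correlations could serve as a check.

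The article fixes the criterion itself, so this is more than a detail left to a fuller document: an analysis plan that adjusted for multiplicity would depart from the published rule.

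**Working it through.** The article gives no number of tests and no error rate for the family, and its sample size rests on feasibility, so there is no figure of its own to reproduce. The check asks what the stated rule delivers when there is no association at all.

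**Inputs from the article**
- Per-test level 0.05 (sidedness not stated; two-sided assumed).
- 15 clinical outcomes.
- 1 to 3 change times.
- 60 patients with PD.

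**Assumption.** The number of key taxa, k, is not given. A range is shown.

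**Formulas**
- Tests: m = k × 15 × change times.
- Expected false links: 0.05 × m. This holds whatever the dependence between tests, provided each test has size 5%.
- Chance of at least one, if the tests are independent: 1 − 0.95^m.

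| Taxa (assumed) | Tests, one time | Expected false links, one time | Chance of at least one, one time | Expected false links, three times |
|---|---|---|---|---|
| 1 | 15 | 0.75 | 54% | 2.25 |
| 3 | 45 | 2.25 | 90% | 6.75 |
| 5 | 75 | 3.75 | 98% | 11.25 |
| 10 | 150 | 7.5 | >99.9% | 22.5 |
| 32 | 480 | 24 | about 100% | 72 |
| 50 | 750 | 37.5 | about 100% | 112.5 |

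To expect 24 or more false links takes 24/0.05 = 480 tests. That means 480/15 = 32 taxa at one time, or 480/45 = 10.7, so 11 taxa, across three.

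**Size of correlation that passes.** The critical value is |rho| = t/√(n − 2 + t²), with t from 58 degrees of freedom. With n = 60 it is about 0.25 at 0.05, about 0.45 at 0.05/150 and about 0.49 at 0.05/750.

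**Simulation.** Spearman correlations were generated under the global null (n = 60, 15 outcomes, 1,000 runs, taxa independent of one another).
- The mean numbers of false links were 7.5, 15.1 and 37.6 for 10, 20 and 50 taxa, in line with the formula.
- With a correlation of 0.5 between outcomes the means were unchanged, but the spread widened. For 10 taxa, the 5th to 95th percentile ran from 2 to 16, against 3 to 12 with uncorrelated outcomes.
- The chance of any false link was 98% to 100% unadjusted. With Benjamini–Hochberg at 5% it was about 4% to 6%.

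**Time analyses.** Each selected taxon or metabolite adds a further 0.05 expected false findings. For an assumed 10 variables that is 0.5, and for 50 it is 2.5.

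**The case against.** The strongest reply is that the study is declared exploratory. *Sample Size* says it is not meant to validate the treatment effect statistically, and the limitations paragraph of the Discussion concedes limited reliability of the comparisons. The correlations are also confined to key taxa, which could be a handful. This stands in part: it lowers the severity, and it argues for false discovery rate control over stricter family-wise control. It does not remove the point. The Discussion speaks of verifying a hypothesis, and its closing paragraph says a demonstrated microbiome change would be the first clinical evidence for the mechanism. The only error-rate risk it names is type II.

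Three stronger readings are tempting, and the article does not support them.
- *Dozens of false links.* This needs at least 32 taxa at one change time or 11 across three. The number of taxa is not stated, so such counts are assumptions.
- *All three change times enter the correlations.* They are defined for the clinical analyses. The correlation sentence does not say which are used, so the three-time column is an upper case.
- *Uncorrected taxon-by-taxon tests of patients against healthy participants.* That subsection says "Differences in gut microbiome between healthy participants and patients with PD will be determined by testing the acquired data for normality" and goes on to name the tests. It does not say whether the variable is a taxon or a summary such as a diversity index, and it sets no threshold.

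The 98% for five taxa also assumes independence. Five of the 15 outcomes are the MDS-UPDRS total and its own parts, so the true figure will differ. The expected counts do not depend on that assumption.

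**Conclusion.** The point holds as a defect in a stated rule and should be fixed. Under P<.05 per test, each key taxon brings 0.75 expected chance links per change time if all 15 outcomes are used. Three to ten taxa at one time give about 2 to 8, and an assumed 50 give 37.5. With five or more taxa, at least one false link is near certain if the tests are independent. A correlation of about 0.25 passes, where Bonferroni over 750 tests would ask for about 0.49.

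These figures rest on the assumed number of taxa, on use of all 15 outcomes and, for the critical values, on 60 patients with data. If the key taxa are picked from the same data, the number of correlations understates the search. By how much cannot be worked out, because no selection rule is given.

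**What to change.** In the microbiome and metabolite subsection, replace the P<.05 criterion with Benjamini–Hochberg control of the false discovery rate at one stated q, for example 0.05. Apply it separately within three families: taxon-by-outcome correlations, taxa over time, and metabolites over time.

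Adjusting only within a set already picked for its results would not control false discoveries. Either count in each family every taxon or metabolite screened, or fix the key taxa and the change times by a rule that does not use the same outcome data.

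Report the number of tests in each family, show nominal P values as descriptive, and label the links hypothesis-generating.

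The cost is small: no new data and little programming. The price is that fewer links will be called significant. The Results section says observation has ended and analysis is under way, so the change must be dated and reported as made after data collection.
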